## Abstract

**Background:**

Although obesity surgery is currently the most effective method for achieving weight loss, not all patients lose the desired amount of weight and some show weight regain. Previous research shows that successful weight loss may be associated with the amount of investment the patient feels that they have made in their operation. For example, those who feel that it has taken more time and effort to organise, has cost more money, has been more disruptive to their lives and has caused pain are more likely to lose weight after their operation. Therefore, it seems as if the greater the sense of investment, the greater the motivation to make the operation a success. The present study aims to build on these findings by encouraging weight loss surgery patients to focus on the investment they have made, thus making their investment more salient to them and a means to improve weight loss outcomes.

**Methods:**

The study involves an open randomised parallel group control trial with patients allocated either to the control or investment intervention group. Using third party blinded randomization, half the patients will be asked to rate and describe the investment they have made in their operation just before surgery then 3 and 6 months after surgery. All patients will record their weight, beliefs about food, intentions to change and actual eating and exercise behaviour at baseline then 3, 6 and 12 months follow up. Patients will be recruited from the bariatric surgery pre-assessment clinic at University College Hospital, London. The primary outcome is to explore the impact of the investment based intervention on patient’s weight and BMI, with secondary outcomes of patients’ beliefs about foods, behavioural intentions and diet and exercise behaviours.

**Discussion:**

It is predicted that the investment intervention will improve excess weight loss post-surgery, together with beliefs about food, intentions to change and actual change in diet and exercise behaviour. This has cost implications for the NHS and other healthcare providers as improved effectiveness of bariatric surgery reduces the health costs of obese patients in the longer term and this simple, easy to administer and low cost intervention could become routine practice for bariatric patients.

**Trial registration:**

ClinicalTrials.gov identifier NCT02045628; December 2, 2013.

## Background

Obesity is caused by people consuming more energy than they expend and is associated with reduced life expectancy and many serious conditions including heart disease, stroke, diabetes, cancer, gallstones, fatty liver disease and sleep apnoea [1,2]. Currently almost two-thirds of UK adults are either overweight or obese with overall costs to society forecast to reach £50 billion per year by 2050 on current trends [2].

Although the most common form of obesity management emphasizes changes in diet and exercise, research indicates that weight loss surgery (WLS) is most effective and this approach is currently recommended for those whose BMI is greater than 40 kg/m2 (or 35 kg/m2 with comorbidities) [3]. A systematic review of WLS [4] concluded that the mean percentage excess weight loss (EWL) for the Roux-en-Y gastric bypass was 67% and for the gastric band was 42% at one year. WLS has also been shown to result in improvements in a number of other patient outcomes including quality of life, mood, subjective health status and perceptions of eating control [5,6].

Although WLS is currently one of the most frequently performed procedures in the US and Europe [7], questions have been raised about the long-term durability of weight loss as research indicates that a substantial proportion of individuals begin to regain lost weight over time [5,8-10]. In response to growing evidence that WLS does not work for everyone research has attempted to understand this variability. In particular, research has explored the mechanisms involved in successful and failed bariatric surgery to highlight how effectiveness could be improved [11,12]. The results indicate that less successful surgery is associated with feeling unprepared for the changes required after surgery, reporting being unsupported in the time following surgery and a sense that although surgery fixes their body, psychological issues relating to dietary control, self-esteem, coping and emotional eating remain neglected. These studies also explored successful weight loss following surgery and reported a role for a reduction in hunger, a decrease in the preoccupation with food and sense of improved control. Such research also highlights a central role for investment and this is supported by other studies using medical and behavioural interventions. For example, bariatric patients reported that success was associated with a feeling that they had made an investment in their operation in terms of factors such as time of work, financial cost, disruption to family and social life, the pain of the surgery and the process of recovery. As one participant said after surgery ‘the amount of pain, the operations performed. Don’t want to do any damage, don’t particularly want the stomach to enlarge anymore which it can do’. Similarly, research indicates that obesity medication may work through the greater investment needed for adherence due to unpleasant side effects [13]. Further, success from behavioural interventions is associated with perceptions of greater investment in attempts to lose weight such as joining self-help groups or attending organised slimming clubs. From this perspective greater investment into weight loss attempts increases the chances of success by motivating the individual to make the most of the efforts they have made so far and encourages them to maximise the consequences of these efforts.

Perceived investment therefore motivates change across all areas of obesity management. This perspective finds reflection in the body of work on the effect of financial incentives on behaviour change with greater costs either facilitating positive behaviours or deterring unhealthy behaviours [14]. It is also parallel to research on the placebo effect which illustrates that placebos which involved greater investment (i.e. bigger pills, expensive treatments, painful interventions, lengthy consultations, greater distances travelled) are more effective that those which are easier to take part in [15]. In line with this approach, a recent pilot study explored the impact of manipulating perceived investment in patients just after they had had bariatric surgery [16]. Patients (n = 98) were recruited from an online support group for bariatric patients and were randomly allocated to either the control or intervention group. Those in the intervention group then completed a simple series of carefully framed questions designed to encourage them to consider the investment they had already made in having their operation. For example, they were asked to rate the procedure in terms of their pain experienced, the time spent organising the operation, the disruption to their family and social life, the time needed to recover and the impact of the recovery process on their family and work. This approach was inspired by recent research exploring the ‘mere measurement’ effect which illustrates that simply completing framed questions can change the ways in which people think and behave [17,18]. The results from this pilot study indicated that the investment intervention resulted in an immediate change in participants’ beliefs about food and their intentions to change their diet and exercise behaviour. By three months follow up the investment group reported losing 7 kg more than the control group (a significant difference). This pilot study was small scale and involved patients post-surgery only. In addition, follow up data was only collected in the short term and attrition was high by this time point (probably due to the online nature of the study). The present study aims to develop this investment based intervention using a larger sample, with a longer follow up and involving assessments at both pre and post-surgery in order to generate a proper baseline. Bariatric surgery is therefore the treatment of choice for obese patients. Not all patients, however, lose the desired amount of weight. Research highlights a role for investment which lends itself to a low cost, easy to administer intervention that may promote successful weight loss in the longer term. Therefore the aim of this study is to evaluate the impact of an investment based intervention compared to usual care on patient weight loss, beliefs and behaviours after bariatric surgery.

## Methods/Design

### Design

The study will involve an open randomised parallel group control trial with patients allocated either to the control or investment intervention group. All participants will complete measures of their beliefs about food, diet and exercise behaviour, intentions to change their behaviour and weight at baseline (2 weeks pre surgery) and at 3, 6 and 12 months follow up. Those in the investment group will complete carefully framed questions designed to raise the salience of the investment they have made in their procedure at baseline the 3 and 6 months after surgery. The content of this intervention will be tailored to the recent experiences of the patient (i.e. pre or post-surgery). This study has received favourable ethical opinions from the Bloomsbury Research Ethics Committee, National Research Ethics Service UK and the University of Surrey Ethics Committee. The structure and reporting of this trial will be guided by the CONSORT statement for clinical trials [19].

### Piloting

A pilot study has already been completed which illustrates that a low cost, easy to administer investment based intervention can change beliefs about food and improve weight loss in bariatric patients [16]. This was based upon previous research and is grounded in research on the mere measurement effect, the impact of incentives and the placebo effect. The present study is an extension of this work using a larger sample, pre and post-surgery interventions and measurements and a longer term follow up.

### Sample

University College Hospital (UCH) in London, UK, offers a NHS based standardised bariatric service for obese patients with a BMI over 40 (or 35 with serious co morbidities). Patients will be recruited if they have been approved for surgery and are attending the hospitals bariatric surgery pre-assessment clinic.

### Inclusion/exclusion criteria

Patients will be included if they consent, are aged 18 or over, have attended the bariatric clinic at UCH, been accepted for surgery and have funding in place (i.e. the CCG has agreed to pay for their surgery). Recruitment will take place over a 14 month period.

### Power calculation

The effectiveness of the proposed investment based intervention has been preliminarily examined in the pilot study conducted by Husted and Ogden [16]. The study showed that with only 98 participants (48 in intervention and 50 in the control groups) there was a significant effect of the intervention on weight loss by 3 months follow up with a mean difference of 7 kg between the groups. This resulted in a small / medium effect size (d = 0.3). The present study aims to assess outcomes up to 12 months thus raising the risk of attrition over time. In addition, the study will have a baseline measure of weight pre surgery rather than after surgery. Therefore, assuming an attrition rate of 40% by 12 months with an alpha of 0.05 and a beta of 0.8 we propose to invite 200 participants (100 in each condition) to ensure that data from at least 120 participants is collected at the 12 months follow up (60 in each group). This should provide statistical power to detect a small to medium difference in weight (controlling for baseline weight) by 12 months follow up.

### Procedure

Two weeks before their operation patients attend the bariatric clinic for routine pre-operative tests. At this point all patients will see the researcher who will explain the trial, obtain consent and randomly allocate the patient to either the control or the investment based weight loss intervention condition.

### Randomisation

Once a patient is consented the researcher will use the third party blinded randomization process provided by the clinical trial unit at the University of Surrey to allocate them to either the investment based intervention condition or the control group, using random number tables according to surgery type.

### Control group

Those allocated to the control group will receive usual care and complete a questionnaire at baseline then 3, 6 and 12 months after bariatric surgery.

### Investment intervention group

Those allocated to the investment based intervention will complete the investment based intervention at baseline (2 weeks pre surgery) then 3 and 6 months post-operatively. This intervention is based on the pilot study [16] and involves participants rating questions relating to the investment they have made in having bariatric surgery as a means to raise the salience of their investment. In particular, the questions will encourage patients to consider the ways in which the surgery has impacted upon them in terms of financial, social, personal and physical costs and focuses on factors such as pain, disruption to their family, social and work lives and financial burden. The investment intervention will be tailored to the recent experiences of the participants. To this end the questions and responses are framed in such a way as to emphasise investment in the process of bariatric surgery in order to optimise the outcomes of the procedure. They will also complete a questionnaire at baseline then 3, 6 and 12 months after surgery.

### Primary outcome measures

BMI and weight: Patients’ weight will be obtained in the clinic to provide the primary baseline and endpoint measure of the trial. This will be collected preoperatively 2 weeks before surgery, immediately after surgery and postoperatively at 3, 6 and 12 months follow up. In addition baseline measures of age, sex, height, type of surgery, educational level, and ethnicity will also be taken.

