### Data analysis

The data will be analysed to explore the impact of the investment based weight loss intervention on patient’s weight and BMI controlling for baseline measures using ANCOVA. Furthermore the impact of the investment intervention will be explored with regard to patients’ beliefs about foods, behavioural intentions and diet and exercise behaviours using repeated measures ANOVA. Finally the data will be analysed to assess the role of changes in beliefs about food, behavioural intentions and behaviour in predicting weight loss by follow up using mediation analysis. Any baseline differences will be included as covariates in the analysis where necessary.

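### The protocol does not consistently fix one primary comparison: weight and BMI are both primary with no visit named, the sizing uses weight by 12 months, and the prediction is for excess weight loss

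*Protocol article*

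**What the plan says.** Five places in the protocol article bear on the primary comparison.

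- **Abstract, Methods:** "The primary outcome is to explore the impact of the investment based intervention on patient’s weight and BMI". Two variables, no time point.
- **Abstract, Discussion:** "It is predicted that the investment intervention will improve excess weight loss post-surgery". Elsewhere excess weight loss appears only in the Background, in figures from a cited review, and in the abbreviation list.
- **Power calculation:** "assuming an attrition rate of 40% by 12 months with an alpha of 0.05 and a beta of 0.8". The 200 invited are meant to leave 120 with data at 12 months, and the difference to be detected is in weight, adjusted for baseline weight, by that follow-up.
- **Primary outcome measures:** the entry is headed BMI and weight, and its sentence has clinic weight taken "to provide the primary baseline and endpoint measure of the trial". The heading words name two variables and the sentence names one. Weight is collected before surgery, "immediately after surgery and postoperatively at 3, 6 and 12 months follow up". No visit is called primary.
- **Data analysis:** the intervention effect is to be explored on "weight and BMI controlling for baseline measures using ANCOVA". Two variables, no visit. Excess weight loss is absent.

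**The concern.** A reader cannot tell from these sections which single result decides the trial. The variable is weight, weight and BMI, or excess weight loss, depending on the section. The visit is 12 months in the Power calculation and open everywhere else.

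The visit matters for more than error rates. The intervention is delivered at baseline, 3 months and 6 months, so weight measured at 3 months can reflect only the baseline session, whereas weight at 12 months follows all three. The visits answer different questions. The pilot's positive result was at 3 months and 40% attrition is expected by 12 months, so an early visit could become the headline unless the primary visit is fixed. At stake are the 5% error rate of the primary claim and the match between that claim and the comparison used to size the trial.

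**Working it through.** **Inputs from the protocol article.** Alpha 0.05 (Power calculation; sidedness not given, two-sided assumed); 60 per arm with 12-month data (Power calculation); follow-up at 3, 6 and 12 months (Primary outcome measures); baseline-adjusted ANCOVA (Data analysis); height taken at baseline (Primary outcome measures).

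**Inputs assumed.** The article gives none of these.
- One quarter of patients are men; mean height 1.77 m (men) and 1.63 m (women), SD 0.07 m.
- Baseline BMI has mean 46 and SD 7, with a floor of 35.
- Mean loss is 15%, 22% and 28% of baseline weight at 3, 6 and 12 months, with SDs of 5, 6 and 8 percentage points.
- The correlation of loss between adjacent visits is r, from 0.5 to 0.95, and r² between 3 and 12 months.
- Excess weight is weight above BMI 25.
- All 60 per arm are observed at every visit.

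**Step 1: the plan's own figures.** 200 × (1 − 0.40) = 120, or 60 per arm, as stated. One test of weight at 12 months should carry a 5% error rate; the simulation gives 4.3-5.2%, consistent with 5% (simulation standard error √(0.05 × 0.95 / 4000) ≈ 0.3 points).

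**Step 2: upper reference.** For k independent tests at 5%, the chance of at least one false positive is 1 − 0.95^k. For k = 2 this is 9.8%, for k = 3 it is 14.3%, and for k = 6 (two variables at three visits) it is 26.5%. Real tests here are strongly correlated, so these are ceilings.

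**Step 3: allowing for correlation.** Null simulation, 4000 runs per row, each test a baseline-adjusted ANCOVA at two-sided 5%. Entries are the chance (%) of at least one significant result.

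| r | Weight, 12 months | Weight or BMI, 12 months | Weight, any of 3 visits | Weight or BMI, any of 3 visits |
|---|---|---|---|---|
| 0.5 | 5.2 | 5.9 | 12.6 | 14.6 |
| 0.7 | 5.2 | 6.0 | 11.9 | 13.5 |
| 0.8 | 4.6 | 5.3 | 10.0 | 11.1 |
| 0.9 | 4.6 | 5.2 | 8.4 | 9.4 |
| 0.95 | 4.3 | 5.0 | 7.0 | 7.9 |

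A direct multivariate normal calculation for three visits gives 12.9%, 11.4%, 10.3% and 8.8% at r = 0.5, 0.7, 0.8 and 0.9, in line with the fourth column.

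**Step 4: where the increase comes from.** Adding BMI to weight at 12 months adds 0.6 to 0.8 points, because BMI is weight divided by a fixed height squared. Opening the visit, for weight alone, adds about 3 to 7 points. Adding BMI on top of the open visit adds a further 1 to 2 points.

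**Step 5: excess weight loss.** If it too were tested, the simulated range would be 6.6-8.1% at 12 months and 10-19% across the three visits. This is an illustration only, since no section plans such a test.

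**The case against.** The strongest reply is that the article already points to one comparison. The Power calculation counts completers at 12 months and speaks of weight adjusted for baseline, which is the ANCOVA named in Data analysis. The Primary outcome measures sentence calls weight, in the singular, the endpoint measure. The 3-, 6- and 12-month list is a measurement schedule and not a list of primary tests. BMI with fixed height is nearly the same outcome on another scale. The article condenses a fuller plan, and a rule for multiple tests may sit in an analysis plan that is not shown.

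Most of this stands, and it limits the point. A reader might infer that a significant result on either variable at any visit would count as primary success, so that the trial's error rate already exceeds 5%. No section says that, and the absence of an alpha rule from this article is not a defect in itself. A reader might also count excess weight loss as a third primary test. It is a prediction in the abstract, not a planned analysis.

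What the reply does not remove is the inconsistency. The sizing implies weight at 12 months but never calls it the one primary test, and the abstract, the outcome heading and the analysis section do not follow it. An unseen plan could add a rule, but it would not correct those statements.

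**Conclusion.** The point holds as an inconsistently fixed primary endpoint, not as proof of an inflated error rate. Variable and visit differ between the abstract, the outcome section, the power section and the analysis section, and the stated prediction is for a measure that is neither listed nor analysed. If each visit were tested at 5%, a false claim on weight or BMI would have a chance of about 8-15% instead of 5%. That range rests on assumed between-visit correlations of 0.95 to 0.5, on the assumed height, BMI and weight-loss distributions, and on treating every visit as a stand-alone primary test. The open visit accounts for most of it; the weight-and-BMI pairing alone is a minor matter.

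**What to change.** State one primary endpoint: body weight at 12 months, compared between the randomised groups by ANCOVA with baseline weight as covariate, as the Power calculation already implies. Include surgery type as a covariate, since the Randomisation section allocates by it. List BMI, percentage excess weight loss (with its reference weight defined) and weight at 3 and 6 months as secondary. Use the same wording in the abstract, Primary outcome measures and Data analysis, and restate the prediction in terms of weight at 12 months. Check that the registry entry and any analysis plan, neither of which is shown, say the same.

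The cost is wording only; no data collection or sample size changes. The small downside is that a result on BMI or at an earlier visit can no longer be claimed as primary success.

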### Secondary outcome measures

Beliefs about food; including hedonic wanting using the Power of Food Scale (PFS) [20], hedonic liking relating to food palatability preference using written representations of food types replicating examples suggested in previous studies [20,21]. Behavioural intentions including patients’ intentions to eat foods high in fat and sugar content and diet and exercise behaviour using measures of snack and meals intake that have been used extensively in previous research [22,23].

### Data analysis

The data will be analysed to explore the impact of the investment based weight loss intervention on patient’s weight and BMI controlling for baseline measures using ANCOVA. Furthermore the impact of the investment intervention will be explored with regard to patients’ beliefs about foods, behavioural intentions and diet and exercise behaviours using repeated measures ANOVA. Finally the data will be analysed to assess the role of changes in beliefs about food, behavioural intentions and behaviour in predicting weight loss by follow up using mediation analysis. Any baseline differences will be included as covariates in the analysis where necessary.

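### Height is collected but not fixed as a covariate in the weight ANCOVA; naming it would be a free, modest gain in precision

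*Protocol article*

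**What the plan says.** - **Data analysis:** the primary analysis covers "weight and BMI controlling for baseline measures using ANCOVA". The baseline measures are not itemised. The section's last sentence allows variables on which the arms differ at baseline to be added as covariates where needed.
- **Power calculation:** the trial is sized to "detect a small to medium difference in weight (controlling for baseline weight) by 12 months follow up". Baseline weight is the only covariate named.
- **Primary outcome measures:** weight and BMI are listed together as primary, and "baseline measures of age, sex, height, type of surgery, educational level, and ethnicity will also be taken".
- **Background:** the surgical effect is given on the excess-weight scale: "mean percentage excess weight loss (EWL) for the Roux-en-Y gastric bypass was 67" percent, and 42% for the band, at one year. The abstract's Discussion also predicts the benefit as excess weight loss.

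**The concern.** Read with the power section, the primary analysis adjusts weight for baseline weight and BMI for baseline BMI. Height then enters the weight model only if the arms happen to differ on it. Imbalance is a poor trigger for a prognostic covariate, because the reason to adjust is that it predicts the outcome, however well the arms are balanced.

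Height may well predict the outcome here. If surgery removes a share of excess weight, then of two patients with the same starting weight the taller has less excess to lose and is expected to end heavier. Without height, that predictable difference stays in the error term of the outcome the trial is sized on. At stake is the width of the confidence interval for the arm difference in weight. The validity of the comparison is not affected.

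**Working it through.** **1. The plan's own figures.**

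Inputs from the Power calculation section: "assuming an attrition rate of 40% by 12 months with an alpha of 0.05 and a beta of 0.8" (the last figure taken as power, the test as two-sided); "This resulted in a small / medium effect size (d = 0.3"); a pilot difference of 7 kg; "we propose to invite 200 participants (100 in each condition").

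- Attrition: 200 × (1 − 0.40) = 120 completers, 60 per arm. This reproduces.
- Size for d = 0.3: n per arm = 2 × (1.96 + 0.842)² / 0.3² ≈ 175, against 60 planned.
- Power at 60 per arm: Φ(0.3 × √(60/2) − 1.96) = Φ(−0.32) ≈ 0.38.
- Reaching about 80% with 60 per arm at d = 0.3 needs a baseline/follow-up correlation of about √(1 − 60/175) ≈ 0.81, which the article does not state.

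The stated power is therefore not reproduced from d = 0.3 alone. That is a separate matter, used here only as a yardstick.

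**2. Why height can matter.**

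Let W₀ be baseline weight, W₁ follow-up weight, h height and p the share of excess weight lost. Take 25 kg/m² as the reference BMI (an assumption).

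- Weight scale: W₁ = W₀ − p(W₀ − 25h²) = (1 − p)W₀ + 25p·h². Height remains after conditioning on W₀.
- BMI scale: dividing by h² gives BMI₁ = (1 − p)BMI₀ + 25p. Height drops out.

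Illustration: two patients of equal W₀, with assumed heights 1.63 m and 1.77 m. Reference weights are 25 × 1.63² = 66.4 kg and 25 × 1.77² = 78.3 kg, a gap of 11.9 kg. Expected follow-up weights differ by 0.67 × 11.9 ≈ 8.0 kg at the bypass mean and 0.42 × 11.9 ≈ 5.0 kg at the band mean.

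**3. How much residual variance height removes.**

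Only the mean EWL figures come from the article; every spread is assumed. W₁ was simulated from the formula above and regressed on W₀ with and without height.

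*Set A.* Heights 1.63 m (SD 0.065) for women and 1.77 m (SD 0.07) for men, 65–80% women, BMI mean 46, SD 6–8, floor 35, EWL SD 12–25 points. Reduction in residual variance:

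- mean EWL 67%: about 5–22%
- mean EWL 42%: about 2–10%
- EWL SD 20 points, both means: about 3–9%

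*Set B.* A single height distribution (mean 1.67 m, SD 0.07–0.09), BMI mean 46, SD 6–8, surgery type in the model for the equal mix:

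| EWL SD (points) | mean 67% | mean 42% | equal mix |
|---|---|---|---|
| 10 | 22.1–30.3% | 10.0–14.5% | 14.3–19.7% |
| 15 | 11.1–16.0% | 4.7–6.9% | 7.4–10.5% |
| 20 | 6.6–9.6% | 2.8–4.0% | 4.3–6.4% |
| 25 | 4.2–6.4% | 1.6–2.6% | 2.9–4.2% |

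The two sets agree. Only the row with the smallest EWL SD, outside Set A's range, goes above 22%. For BMI adjusted for baseline BMI the gain from height is 0% throughout.

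**4. What that is worth.**

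Power for 7 kg at 60 per arm is Φ(7 / (SD × √(2/60)) − 1.96). At an EWL SD of 20 points in Set B:

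- Largest gain (67% EWL): residual SD falls from 13.4 to 12.7 kg and power rises from 0.819 to 0.855. The precision of 120 completers is reached with 120 × (1 − 0.096) ≈ 108.
- Smallest gain (42% EWL): 12.4 to 12.3 kg, power 0.869 to 0.878, and 120 × (1 − 0.028) ≈ 117.

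These powers are for 7 kg against a residual SD of about 13 kg, a standardised difference near 7/13.4 ≈ 0.52. They do not confirm power at d = 0.3.

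**5. Where the gain disappears.**

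- If loss is a share of total weight unrelated to BMI, W₁ = (1 − q)W₀ with q the share lost, and height adds nothing.
- If baseline BMI is already in the weight model, height is largely carried, because h² = W₀/BMI₀. Adding baseline BMI instead of height gave 5.2–21.3% against 5.3–21.9%, about 97% of the gain.

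**6. Against the sizing gap.** A 9.6% cut takes 175 per arm to about 175 × 0.904 ≈ 158. A 22% cut takes it to about 175 × 0.78 ≈ 137. Both are far from 60.

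**The case against.** The strongest reply is that the article does not leave height out. The words used for the ANCOVA adjustment are the same words that introduce the list containing height under Primary outcome measures, and the sentence on baseline differences may have been meant for the secondary and mediation analyses. A full covariate list is also commonly left to an analysis plan that is not shown. This stands in part. A reader might infer that the plan excludes height, but the text does not say so. What can be said is that height is not named, and that the reading consistent with the power section does not include it.

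Two further replies stand. If the phrase means that both baseline weight and baseline BMI enter the weight model, almost nothing is lost. And a mean percentage EWL does not show that individual patients follow the excess-weight formula with p unrelated to height; reporting on that scale does not establish the model.

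BMI as a co-listed primary outcome already avoids the inefficiency, but it does not settle the point, because the trial is sized on weight. A reader might also infer that omitting height is what could make the weight and BMI results disagree. In one simulated bypass-only scenario (EWL SD 20 points, 7 kg effect), the 5% verdicts differed in about 7% of trials. Naming height does not settle which of the two outcomes governs, so that is a separate question.

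**Conclusion.** The point holds as a modest efficiency suggestion. It is neither an error in the plan nor a source of bias. If the weight model contains baseline weight only, and if loss follows the excess-weight scale used in the Background, then fixing height as a covariate reduces residual variance by about 2–22% for an EWL SD of 12–25 points. The central range, at an EWL SD of 20 points, is about 3–9%, or roughly 1–4 power points. No figure in the article fixes the spreads of height, BMI or EWL, so the size is conditional on those assumptions.

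Two stronger readings are tempting and unsupported: that the omission makes the weight analysis wrong, and that adding height would rescue the sample size. Randomisation protects the comparison either way, and the gap between 60 and 175 per arm at d = 0.3 is far larger than any gain found here. Low priority.

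**What to change.** In the Data analysis section (or the analysis plan, if one exists), replace the general phrase with a named list. For example: weight will be analysed by ANCOVA adjusted for baseline weight and baseline height, and BMI by ANCOVA adjusted for baseline BMI, with these covariates fixed in advance whether or not the arms differ on them. Adjusting weight for baseline weight and baseline BMI serves practically the same purpose. The phrase in the Power calculation section should then match.

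The cost is one sentence and one degree of freedom. Height is already collected at baseline, so no new data or patients are needed. The sample-size justification needs its own attention.
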